#### *Gender-specific stress*

Gender-specific stress will be measured with the Dutch translation of the Feminine Gender Role Stress (FGRS) for women and the Masculine Gender Role Stress (MGRS) for men [51]. Parents will be asked to express the extent to which they perceive several situations as stressful. The FGRS consists of subscales for non-emotional relationships, bodily unattractiveness, victimization, assertive behavior and non-caring behavior. The MGRS consists of subscales for bodily inadequateness, emotional expressionlessness; being subordinate to women, intellectual inferiority and not being able to perform. Both questionnaires use a 6-point scale and consist of 40 items. Internal consistency is good (Table 2).

#### *Perceived social support*

Perceived social support will be measured with the Social Support Inventory for adults (Called *Sociale Steun Lijst* (SSL) in Dutch) [37]. Parents will be asked to express their perceived social support on three dimensions: SSL-Interactions (SSL-I), SSL-Discrepancies (SSL-D) and SSL-Negative interactions (SSL-N) The dimensions SSL-I and SSL-D both consist of seven subscales (daily emotional support, emotional support in problem situations, appreciation, instrumental interactions, social companionship, informative support) and has 34 items. The SSL-N has 7 items. All dimensions use a 4-point scale. Internal consistency is good (Table 2).

#### *Coping*

Coping will be measured with the Coping Inventory for Stressful Situations (CISS) [41]. Parents will be asked to rate the extent to which they use several coping skills in stressful situations on three subscales: problem-focused coping, emotion-focused coping and avoidance. The CISS uses a 5-point scale and consists of 48 items. Internal consistency is good (Table 2).

#### *Life events*

Life events will be recorded with the Dutch *Vragenlijst Meegemaakte Gebeurtenissen* (VMG) [52]. Parents will be asked to report if, how many times and when for the last time, various positive or negative life events have occurred in the child’s life. In addition, if a life event has occurred, the parent will be asked to rate the child’s perception of it as positive or negative. The VMG consist of 24 items. Internal consistency is good (Table 2).

#### *Neighborhood perception*

Neighborhood perception will be measured with the Dutch translation of the Neighborhood Characteristics Scale [53]. Parents will be asked to express their agreement with several hypotheses concerning their neighborhood on two subscales: physical neighborhood disorder and social neighborhood disorder. The Neighborhood Characteristics Scale uses a 5-point scale and consists of 18 items. The original scale has good psychometric properties (α .92). Information on the psychometric properties of the Dutch translation is not available.

In addition to the above outcome measures, parents will be asked to complete a recording form to collect information on gender, age, ethnic background, parental education level, current living situation and employment status, net income, financial problems, alcohol use and health care information.

### Analyses

First a non-response analysis, using univariate analysis, will be carried out to compare characteristics of the included participants with the characteristics of the entire population of children aged 5–16 years reported to the seven participating AMKs within the recruitment period of this study. The following characteristics will be studied: age of the child, gender of the child, ethnicity, living situation, type of maltreatment as verified by the AMK, outcome of the AMK procedure.

Missing data at follow-up will be imputed using regression imputation. Prior to the analyses the possible influence of (1) the different AMKs (as families will be derived from 7 AMKs), and (2) the time between the report to the AMK and the completion of the questionnaires will be examined.

The first research question, regarding the mental health and quality of life of maltreated children over a 1.5 year period, will be addressed using a longitudinal multi-level analyses (measurements nested within respondents, i.e. children and parents/caregivers, respectively) to assess changes in mental health and quality of life over time [54]. The second research question, regarding the influence of relevant determinants on the mental health and quality of life of maltreated children, will be addressed by exploring the potential effects of these determinants on the outcome variables by testing the interaction between potential effect modifiers at T0 and the outcome variables at Tf-upx (where 'f-upx’ indicates the successive moments of measurement during follow–up).

To answer the third research question, regarding differences in mental health and quality of life outcomes between children from families of Dutch origin with children from families originating from Morocco and Suriname, 'ethnicity’ will be entered as a covariate in the analysis.

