### Recruitment and sample size

Parent–child dyads will be recruited from seven AMKs in the Netherlands. All AMKs in the four largest cities (Amsterdam, Rotterdam, The Hague, and Utrecht) will be approached to participate in the recruitment for the study, in view of their high percentage of residents of Moroccan and Suriname origin. An additional three large AMKs will be asked to take part in the recruitment phase of the study, taking the level of urbanization into account, to ensure that the sample is representative of Dutch society. The study will focus on children aged between 5 and 16 years, as approximately 70% of all reports to AMKs concern children in this age range [35]. In addition, the study will focus on reports to AMKs of physical and/or emotional abuse, physical and/or emotional neglect and/or sexual abuse, which account for about 70% of all reports to AMKs [35]. Families that meet the inclusion criteria will be approached by phone by an AMK employee within three months after the report was filed with the AMK. In this phone call, they will provide general information about the study, and will invite one parent and one child per family to participate.

Based on expert opinion, we expect a participation rate of 5%. This low expected rate is due to the delicate subject of the study: participants will be recruited shortly after a suspected child maltreatment report, so people might refuse to participate due to the perceived accusation and/or perceived stigmatization and/or stress because of the report to the AMK. In addition, we are expecting obstacles in the recruitment process, for instance because there is often no phone number in the AMK records, people may not be available when the phone call is made, people may not be able to speak Dutch. If a parent–child dyad is willing to participate, an appointment with a member of the research team will be made at a time and place of the families’ choosing (which in most cases will probably be a home visit). During this visit, prior to starting to complete the questionnaire, parents and children will be asked to give written informed consent for their participation. Parents will also be required to give informed consent for the participation of their child.

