After the baseline assessment, an estimated 40% of the participants are expected to be lost to follow-up. To minimize loss to follow–up, parents and children will be asked to write down various types of contact information on the informed consent form, e.g. both home and mobile phone numbers, and email addresses. If phone numbers are no longer valid at follow-up, an email or letter will be sent to the last known home address with the request to contact the research team. In case of no response, a member of the research team will visit the family at their last known address to check if they have moved.

This study aims to examine differences in outcomes when comparing children from families of Dutch origin with children from families originating from Morocco and Suriname. To prevent numbers that are too small to allow a useful analysis, we will oversample families originating from Morocco and Suriname. To this end, extra time will be invested in reaching these families, even beyond the times of the day when AMK employees would normally make recruitment calls. A separate list with phone numbers of eligible Moroccan and Suriname families will be printed, and a Moroccan AMK employee will call the Moroccan families to minimize the risk of refusal to participate due to a possible language barrier. Overall, we expect about 150 parent–child dyads to be available for the last assessment 1.5 years after the report to the AMK.

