This study also has several limitations. First, selection bias cannot be ruled out. Participation is voluntary and families will be recruited shortly after a report of suspected child maltreatment has been filed with an AMK. This can be expected to be a stressful time for most families. In addition, families might be inclined to refuse participation in view of the perceived accusation and/or stigmatization by the child maltreatment report [57]. This may make it harder to find participants for this study, which may lead to a risk of selection bias. To increase the likelihood of success, the researchers will remain in close contact with the participating AMKs during the recruitment process, so they can adjust the process if necessary. In addition, a non-response analysis will be performed to examine the presence of this possible selection bias. Secondly, there is a risk of considerable loss to follow-up. One reason may be that families of maltreated children tend to move more frequently than non-maltreated children and their families [58]. Families may forget to forward their new address and phone number. To minimize loss to follow-up due to changes in contact information, participants will be asked to provide various kinds of contact information. Another possible reason is that many families reported to AMKs are 'multi-problem’ families [59], so there might be new and/or additional problems at follow-up which might cause families to drop out of the study.

To conclude, this study will be the first to provide information on mental health and quality of life outcomes of maltreated children over a 1.5 year period after being reported to an AMK. In addition, it will explore determinants that influence mental health and quality of life outcomes, and will provide information on the influence of ethnicity on maltreatment outcomes. Results will contribute to the knowledge that is required to provide high-quality care to maltreated children.

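### With 5% participation expected, the planned check can show selection on six measured characteristics, but no stated analysis uses it to correct the estimates for the first research question

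*Protocol article*

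**What the plan says.** Under Recruitment and sample size the article states "we expect a participation rate of 5" per cent, attributing this to the sensitive subject and to families who cannot be reached. It adds that "an estimated 40% of the participants are expected to be lost to follow-up" and that "we expect about 150 parent–child dyads to be available for the last assessment". The same section plans to oversample families of Moroccan and Surinamese origin through extra calling effort.

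The Analyses section opens with the selection check: "First a non-response analysis, using univariate analysis, will be carried out to compare characteristics of the included participants". The reference group is every child aged 5–16 on whom the seven centres received a report while recruitment ran. Six characteristics are listed: "age of the child, gender of the child, ethnicity, living situation, type of maltreatment as verified by the AMK, outcome of the AMK procedure". The first research question is then addressed by a longitudinal multilevel model of change over time, with no weights and none of the six characteristics named. Ethnicity enters as a covariate for the third research question only.

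The Discussion concedes that selection bias cannot be excluded. It offers two responses: close contact with the reporting centres during recruitment "so they can adjust the process if necessary", and the comparison itself, described thus: "a non-response analysis will be performed to examine the presence of this possible selection bias".

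Under Target population, dyads whose maltreatment is not confirmed are removed before the first follow-up, so the final sample is restricted to verified cases.

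**The concern.** The first research question is descriptive: how maltreated children fare, and how that changes over 1.5 years. For such a target the make-up of the sample feeds directly into the answer. When about 19 of 20 families are expected not to take part, make-up is a leading threat, and the article says so.

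The article names the threat, the method, the variables and the purpose of the check, but that purpose stops at detection. If participants differ from the reported population in age, living situation or type of maltreatment, and these are related to mental health or quality of life, the estimates carry the difference. Yet the comparison already requires the population figures that a correction would use. Oversampling by origin adds a known departure that needs no test to reveal it and that also stays in any overall estimate.

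**Working it through.** **Implied numbers.** The article gives no power calculation and no baseline or approached number, so there is no figure to reproduce. From its own inputs: 150 / (1 − 0.40) = 250 dyads at baseline, and 250 / 0.05 = 5,000 families approached. This assumes that the 40% covers all losses after baseline; the article does not say whether it includes dyads removed as unverified.

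**What the comparison detects** (assumed two-sided 0.05; 250 against 4,750; a characteristic held by 50%).
- SE of the difference = √[0.25 × (1/250 + 1/4,750)] = 0.0324.
- 5 points: 0.05 / 0.0324 = 1.54; power Φ(1.54 − 1.96) ≈ 34%.
- 10 points: 0.10 / 0.0324 = 3.08; power ≈ 87%.
- Minimum difference at 80% power: 2.80 × 0.0324 = 9.1 points. A much larger reference population hardly matters: 2.80 × √(0.25/250) = 8.9 points.
- If only the 150 completers are compared, power is 22% for 5 points and 68% for 10.
- Six independent tests give at least one false flag with probability 1 − 0.95⁶ = 26.5%.

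**What stays in a mean level.** Bias = imbalance × outcome gap between the groups. The gap is assumed to be 0.2–0.8 SD. SE of a mean with 250 children = 1/√250 = 0.063 SD.

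| Imbalance | Gap | Bias | Bias / SE | Coverage of a 95% interval |
|---|---|---|---|---|
| 5 points | 0.5 SD | 0.025 SD | 0.40 | 93% |
| 10 points | 0.2 SD | 0.02 SD | 0.32 | 94% |
| 10 points | 0.5 SD | 0.05 SD | 0.79 | 88% |
| 10 points | 0.8 SD | 0.08 SD | 1.26 | 76% |
| 20 points | 0.5 SD | 0.10 SD | 1.58 | 65% |

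For change over time the relevant gap is the difference in change between the groups. If that is zero, the bias in change is zero.

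**Oversampling.** The Background gives 4.9% and 4.1% of all reports in 2012 for the two groups, 9.0% together. These are national shares; the seven centres may differ. If each group made up 10%, 15% or 20% of the sample (assumed), the combined excess is 11, 21 or 31 points. At a 0.5 SD gap the shift in an overall mean is 0.055, 0.105 or 0.155 SD.

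**Cost of weighting.**
- Non-response: take logit p = a + σz with z standard normal and mean participation P = 0.05. The design effect is P × E(1/p) = 0.05 × [1 + exp(−a + σ²/2)]. For σ = 0.3 (a = −2.98) it is 1.08; for σ = 0.5 (a = −3.06) it is 1.25. The SE rises by √1.08 to √1.25, about 4% to 12%. Both σ values are assumptions.
- Oversampling: the design effect is Σ(population share² / sample share). At 10% each: 0.049²/0.10 + 0.041²/0.10 + 0.91²/0.80 = 1.08. At 15% each it is 1.21 and at 20% each 1.40, so the SE rises by 4%, 10% or 18%.
- If the two sets of weights were unrelated, the effects would roughly multiply: 1.08 × 1.08 = 1.17 to 1.25 × 1.40 = 1.75, or SE +8% to +32%.

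**The case against.** **An article may leave the follow-up step to a full analysis plan.** This is partly right. The text is silent on what happens after the comparison, so a reader who infers that the outcome models will be run unchanged whatever it shows goes further than the document. What stands is narrower: the check is given a purpose, that purpose is detection, and no consequence is stated.

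**Moderate selection would not go unnoticed.** This is correct. A reader might infer from the low participation rate and the univariate method that it would, but the numbers say otherwise. Suppose participants differ by 0.28 SD on an overall participation score, which is what σ = 0.3 implies. Spread evenly over six independent characteristics, that is 0.28/√6 = 0.114 SD each. Power is about 42% per test, and the chance that at least one test flags is 1 − 0.58⁶ ≈ 96%. What is often missed is a small imbalance on a single characteristic.

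**The first question concerns change, and a constant level shift cancels in change.** This also stands. The bias figures above are for levels. Bias in change arises only if the selected groups change differently, and the documents give nothing from which to estimate that.

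**The characteristics are not wholly unused, and there is another response.** Ethnicity is a covariate for the third question, and recruitment can be adjusted. Neither corrects the first-question estimates.

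**Weighting on the six characteristics against the stated population would not work as it stands.** True, and this shapes the fix. The reference population includes unconfirmed and no-maltreatment cases, which have no chance of being in the final sample, so weights on verified type and procedure outcome would be undefined for them. Nor does the article say whether the population data are child-level or aggregate.

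**The selection most feared, on stigma and stress, is unmeasured.** True. Weighting removes only the part explained by the measured characteristics.

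**Conclusion.** The point holds in this form: at 5% expected participation, the only analytic response stated is a univariate comparison meant to show whether selection bias is present, and no stated analysis uses its result to correct the first-question estimates. Measured imbalance, including that from oversampling by origin, therefore stays in the overall levels and may stay in the changes. Large imbalances would usually be flagged (about 87% power at 10 points, about 34% at 5 points, with the implied 250 participants), but flagging does not remove them.

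The size rests on assumptions. With outcome gaps of 0.2–0.8 SD, a 10-point imbalance biases a mean level by 0.02–0.08 SD and lowers interval coverage to between 94% and 76%. No figure is supported for change. The documents do not show that the main estimates will be materially biased; they show that a measured bias would have no stated remedy. This is a worthwhile improvement to the analysis and does not invalidate the design.

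**What to change.** 1. Compare participants with eligible, verified cases at the seven centres, matching the restriction under Target population. Otherwise verified type and procedure outcome differ by design and not only through non-response.
2. Report standardised differences for the six characteristics and do not rest the conclusion on significance tests.
3. Present first-question levels and changes both unweighted and weighted. Rake to the population margins if only aggregate data are available, or use stabilised inverse-probability-of-participation weights from one multivariable model if child-level data are available. The weights should also cover the oversampling by origin. Because that oversampling works through extra calling effort and not fixed sampling fractions, its weights must come from the population margins.
4. State that weighting cannot remove selection on unmeasured factors such as stigma, stress or severity.

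The cost is some added analysis using figures that the comparison already needs, provided they can be restricted to eligible, verified cases. Weighted estimates lose precision: SE about 4–12% larger for non-response under the assumed participation spread, and more once the oversampling is undone (design effect about 1.08–1.40 for that part under assumed sample shares). Keeping the unweighted results alongside lets readers see the trade-off.

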### Target population

Children aged between 5 and 16 years and their primary caretaker will be recruited to participate in this study shortly after the report is filed with the AMK. Children younger than 5 years old are excluded from the study, as this study will rely on self-report as much as possible. Studies have shown that children from the age of 5 are able to reliably self-report on their own health status [34]. Only one child per family will be asked to participate. When a report to the AMK relates to more than one child of the same family, the oldest child within the age range will be included. Additional criteria for inclusion in the study are: (1) a report to an AMK about physical and/or emotional abuse, physical and/or emotional neglect and/or sexual abuse, (2) sufficient verbal and cognitive capacities of both parent and child, as the study will use mainly self-report methods for data collection, and (3) no intention to leave the Netherlands within the next 1.5 years, in view of the follow-up period. All families meeting these criteria will be approached by phone within three months after the report to the AMK. During this phone conversation, an AMK employee will screen the potential participants for verbal and cognitive capacities.

This study will focus only on children for whom maltreatment is verified during the AMK investigation. The maltreatment verification status will be established in a multi-disciplinary meeting at the end of the AMK investigation. At the time when eligible participants are first approached by phone, most reports will still be under AMK investigation, so the families’ maltreatment status will not be known at the time of study inclusion. Parent–child dyads for whom maltreatment is not confirmed, or dyads that are given a 'no maltreatment’ status, will be excluded from the study sample before the first follow-up assessment six months later.

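### The non-response analysis uses a comparison group that includes children who could never have taken part, so it mixes eligibility with non-response

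*Protocol article*

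**What the plan says.** **The comparison.** The Analyses section opens with it: "First a non-response analysis, using univariate analysis, will be carried out to compare characteristics of the included participants" with those of "the entire population of children aged 5–16 years reported to the seven participating AMKs within the recruitment period of this study". Six characteristics are listed: "age of the child, gender of the child, ethnicity, living situation, type of maltreatment as verified by the AMK, outcome of the AMK procedure".

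**Its purpose.** The Discussion names voluntary participation and refusal as the source of possible selection bias, and then says that "a non-response analysis will be performed to examine the presence of this possible selection bias".

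**Who can be a participant.** Target population requires a report of one of the listed kinds of abuse or neglect. Recruitment and sample size says of these kinds: "which account for about 70% of all reports to AMKs". Target population adds "This study will focus only on children for whom maltreatment is verified during the AMK investigation", and dyads without confirmed maltreatment "will be excluded from the study sample before the first follow-up assessment six months later". Where a report concerns several children of one family, "the oldest child within the age range will be included". Sufficient verbal and cognitive capacity and no plan to leave the country are also required.

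**Ethnic origin.** Recruitment and sample size plans to oversample Moroccan and Surinamese families through extra calling time, a separate phone list and a Moroccan caller.

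**The concern.** A child outside the inclusion criteria was never invited and cannot be a non-responder. The planned reference group nevertheless contains such children, and the analysis is univariate, so nothing separates them from families who refused or were not reached. A difference could then reflect eligibility alone, and similarity could come from two opposing influences.

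Expected participation is only 5%, and this is the only check on selective participation that the article describes. What is at stake is how that check is read. The longitudinal analysis of mental health and quality of life does not depend on it.

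**Working it through.** **Scale.** The non-response analysis has no figure of its own. The nearest stated figure, about 150 dyads at the last assessment, cannot be derived forward because the number of eligible families is not given. Working backward, with 40% taken as the total loss: 150 / (1 − 0.40) = 250 dyads at baseline. At 5% participation, 250 / 0.05 = 5,000 families approached. If listed types make up 70%, the reference group has roughly 5,000 / 0.70 = 7,143 members. These numbers serve only to set a scale.

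Each listed characteristic is now set against the eligibility rules, supposing that participation among eligible families is random.

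**Age.** The direction follows from the oldest-child rule. The size needs assumptions: in-range ages uniform from 5 to 17 (a 16-year-old counts until the 17th birthday), siblings' ages independent, and one to three in-range children per family.

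- The mean age of all children is 11.
- The mean age of the oldest of k children is 5 + 12·k/(k+1), which gives 11, 13 and 14 for k = 1, 2 and 3.
- With 80/15/5% of families having 1/2/3 children: 0.80·11 + 0.15·13 + 0.05·14 = 11.45, a shift of 0.45 years.
- With 60/30/10%: 6.6 + 3.9 + 1.4 = 11.9, a shift of 0.9 years.
- With 40/40/20%: 4.4 + 5.2 + 2.8 = 12.4, a shift of 1.4 years.

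The SD is 12/√12 = 3.46, and the standard error is 3.46·√(1/250 + 1/7,143) = 0.223. The chance of a two-sided 5% test flagging the difference is Φ(shift/0.223 − 1.96): about 52%, 98% and nearly 100%. Independent ages imply a mean gap of 12/3 = 4 years between two siblings. Closer spacing would give smaller shifts.

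**Verified type of maltreatment.** Eligibility depends on the type in the report, and about 1 − 0.70 = 30% of all reports fall outside the listed types. The analysis compares the type verified later by the AMK. The two are presumably related, so a difference is likely, but the link is not stated and no size follows.

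**Outcome of the AMK procedure.** Participants are kept only if maltreatment is verified; the reference group keeps unverified reports. Outcomes such as referral probably differ between the two. Neither the verification rate nor the definition of outcome is given, so no size follows.

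**Ethnicity.** Moroccan and Surinamese families account for 4.9% + 4.1% = 9.0% of reports (Background). The extra effort raises their chance of being reached. As an illustration, if these families agreed half as often but the effort doubled their yield, then 0.5 × 2 = 1 and their share would stay near 9%. Selective refusal would not show.

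**Gender and living situation.** Gender, and perhaps living situation, are less tied to the eligibility rules.

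**With an eligible comparison group.** If the group is limited to children who could have been invited and the other characteristics are compared within ethnic strata, random participation produces no expected difference, and each test rejects at its nominal rate.

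**The case against.** The strongest reply is that the size of the distortion is mostly unknown, and that stronger statements a reader might infer do not follow from the text. Most of this stands:

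- **0% against 30% ineligible types.** The 70% concerns reported type, over all reports and all ages. The listed characteristic is verified type, and nothing says that a participant's verified type must be one of the listed kinds.
- **100% against fewer verified.** Verification status is not one of the six characteristics. Children without verified maltreatment have no verified type, so that variable may already be confined to verified cases. Dyads are also removed only after baseline, so it is unclear whether the included participants are counted before or after removal.
- **Ethnicity shifted by the sampling scheme.** All eligible families are to be approached. The oversampling works through contact effort and not through a different sampling fraction, so a shift would be a real difference in response, partly produced by that effort.
- **Participants inside the reference group.** They make up about 5% or less (250 / 5,000), which is negligible.
- **The check cannot detect selection bias at all.** This goes too far, because gender and perhaps living situation remain informative.

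It can also be said that a comparison with all reported children properly describes representativeness, and that it feeds no estimate or weighting. Both are true. But the article calls it a non-response analysis and relies on it to examine bias from voluntary participation, and for that purpose the group is wrong. This is a choice that the article states, not a detail left to a fuller plan.

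**Conclusion.** The concern holds in limited form. The reference group is restricted only by age, centre and period, while participants are also restricted by report type, verification and the oldest-child rule. Eligibility and non-response are therefore mixed, and the comparison is a poor test of the selection bias named in the Discussion.

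Only the age difference follows directly from the rules. Its size of about 0.45 to 1.4 years rests on assumed sibling patterns and independent ages. Differences in verified type and AMK outcome are probable but cannot be sized. The ethnicity comparison combines willingness with recruitment effort. The change is worth making because it is cheap and makes the stated check interpretable; the main outcome analysis is not affected.

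**What to change.** For the selection-bias check, define the comparison group as non-participating children reported to the seven AMKs in the recruitment period who meet the eligibility criteria recorded in AMK files: a listed report type, verified maltreatment, and the oldest child in the age range per family where sibling links are recorded. Apply the same verification rule to the participants in this comparison. Report the other characteristics within ethnic-origin strata, so that the extra recruitment effort does not carry over into them.

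The comparison with all reported children may be kept, labelled as a description of representativeness.

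**Cost.** A filter on AMK data whose use is already planned, and a change of wording; no new participants, measures or visits. The filter is incomplete: verbal and cognitive capacity is screened in the recruitment call, and it and the intention to leave the country may not be recorded for families who were not reached. The report should say that only recorded criteria were applied. Whether the files hold sibling links has to be confirmed with the AMKs.

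### Regression imputation of follow-up data, with 40% loss expected, understates the uncertainty of change over 1.5 years; for determinants and ethnicity the error depends on an unstated imputation model

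*Protocol article*

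**What the plan says.** The Analyses section fixes the handling of missing values in one sentence: "Missing data at follow-up will be imputed using regression imputation". It does not mention repeated imputations, residual draws, pooling or the predictors to be used.

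The three research questions are then answered from the follow-up outcomes:

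- **Change over time (main objective):** "longitudinal multi-level analyses (measurements nested within respondents".
- **Determinants:** "testing the interaction between potential effect modifiers at T0 and the outcome variables at Tf-upx".
- **Ethnicity:** entered as a covariate.

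Under Recruitment and sample size the article states: "After the baseline assessment, an estimated 40% of the participants are expected to be lost to follow-up". It adds that "we expect about 150 parent–child dyads to be available for the last assessment 1.5 years after the report to the AMK". The Discussion lists considerable loss to follow-up among the limitations.

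**The concern.** In its usual meaning, regression imputation replaces each missing value by the prediction from a fitted regression. Analysed as real data, these values have no residual scatter and count as full observations. The residual variance is too small, the sample size is too large, and confidence intervals are too narrow.

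The step is also unnecessary for the outcomes. A multi-level model of repeated measurements accepts children with different numbers of waves. Fitted by likelihood, it is valid under missing at random without filling anything in.

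At stake are the main conclusion on change after the report and, depending on the imputation model, the determinant and ethnicity findings. The Discussion intends the determinant results to identify the most vulnerable children and the factors that can be influenced.

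**Working it through.** The article gives no alpha, power or effect size, so there is no power figure to reproduce.

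**Inputs from the article.** 40% loss after baseline; about 150 dyads at the last assessment; four assessments.

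**Derived.** Baseline = 150/0.60 = 250 dyads. This number is not stated. About 100 of 250 last-wave values would be imputed.

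**Assumed.** Loss at random, unit variance at each wave, correlation r between waves.

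**1. Mean change from baseline to last wave, deterministic imputation from baseline.** Let f be the fraction observed and N the baseline number.

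- True variance × N = (1 − r²)/f + (1 − r)²
- Variance as reported × N = f(1 − r²) + (1 − r)²

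N cancels, so the ratio does not depend on the derived 250. For r = 0.6 and f = 0.60:

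- True: 0.64/0.60 + 0.16 = 1.2267
- Reported: 0.60 × 0.64 + 0.16 = 0.5440
- SE ratio: √(0.5440/1.2267) = 0.67
- Type I error at nominal 5%: 2 × [1 − Φ(1.96 × 0.67)] ≈ 19%

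| r | true × N | reported × N | SE ratio | type I error |
|---|---|---|---|---|
| 0.3 | 2.0067 | 1.0360 | 0.72 | 16% |
| 0.4 | 1.7600 | 0.8640 | 0.70 | 17% |
| 0.6 | 1.2267 | 0.5440 | 0.67 | 19% |
| 0.8 | 0.6400 | 0.2560 | 0.63 | 21% |

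**2. One random residual added to each prediction.** The true variance × N gains (1 − f)(1 − r²), and the reported variance × N becomes (1 − r²) + (1 − r)². At r = 0.6 these are 1.2267 + 0.2560 = 1.4827 and 0.80. The ratio is √(0.80/1.4827) = 0.73 and type I error is about 15%.

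**3. Four waves, as in the design.** Simulation under no effect: 250 dyads, r = 0.3, 0.5 or 0.7, 20% in the minority group (assumed), imputation on group and earlier waves, 600 runs per setting. Graded loss was 20/30/40% at the three follow-ups. Early loss was 40% at all three (r = 0.5 only). Time contrasts are the slope, ethnicity-by-slope and last-minus-first change.

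| Method | Loss | Contrast | SE ratio | type I error |
|---|---|---|---|---|
| Deterministic | graded | time contrasts | 0.68–0.74 | 13–19% |
| Deterministic | early | time contrasts | 0.63–0.65 | 21–22% |
| Deterministic | graded | ethnicity main effect | 0.85–0.91 | 7–11% |
| Deterministic | early | ethnicity main effect | 0.83 | 10.5% |
| One random draw | both | time contrasts | 0.71–0.78 | 13–17% |
| Multiple imputation, 20 sets, Rubin's rules | both | all | 0.96–1.05 | 3.7–6.5% |

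**4. Determinant effect on the last-wave outcome, adjusted for baseline, determinant unrelated to baseline.**

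- *Determinant in the imputation model.* The true variance is proportional to 1/f and the reported variance to f, so the SE ratio equals f = 0.60. Type I error is 2 × [1 − Φ(1.96 × 0.60)] ≈ 24%. Simulation agrees.
- *Determinant left out.* Imputed values carry none of its effect, so a true 0.20 becomes 0.60 × 0.20 + 0.40 × 0 = 0.12. Under no effect the SE is about right: in simulation the ratio was 1.00–1.01 and type I error 4.5–5.3% for r of 0.4 to 0.8.

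**The case against.** **Single imputation is inferred.** The article is a condensed text, and the number of imputations and pooling are details that a full plan often holds. But the article does name a method, and the ordinary meaning of that name is single imputation. At this level of loss the sentence as it stands is wrong, not just brief.

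**The scope is open.** The text does not say whether wholly missed waves are imputed or only gaps in completed questionnaires. The Target population section also removes unverified dyads before the first follow-up, and the 40% may include them. If only 20% of last-wave values were imputed, r = 0.6 would give 0.64/0.80 + 0.16 = 0.96 against 0.80 × 0.64 + 0.16 = 0.672, a ratio of 0.84 and type I error of about 10%. The error is smaller but still about twice nominal.

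**Stronger readings that the article does not support.** A reader might infer that standard errors are too small in every outcome analysis. They are not if a determinant is left out of the imputation model: the fault is then attenuation. An ethnicity main effect averaged over waves is only modestly affected. Baseline descriptions and the non-response comparison use no imputed values. A reader might also infer that AMK (reporting centre) information is ignored in the imputation, but the article lists no predictors either way.

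**Outcome-related drop-out does not favour one method.** The Discussion names moving and new family problems as possible reasons for loss. If these depend on unobserved outcomes, a likelihood fit under missing at random is biased too.

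**This is an observational cohort without a stated alpha, and the determinant work is exploratory.** That lowers the stakes of a single p-value, but confidence intervals for the main objective would still be too narrow.

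**Conclusion.** The point holds for the main objective. On the ordinary reading, standard errors for change over 1.5 years are about 0.63 to 0.74 of their true size, with type I error of about 13% to 22%. The upper end needs high correlation or all loss before the first follow-up. These sizes rest on 40% of last-wave values being imputed, loss at random, and assumed correlations of 0.3 to 0.8. The direction holds for deterministic imputation and for a single random draw.

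For determinants and ethnicity the article does not settle which error arises. Including the variable in the imputation model gives overconfident tests; omitting it biases the estimate towards zero. Neither is acceptable, so the sentence should be replaced and not just expanded.

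**What to change.** Delete the regression-imputation sentence for the outcomes. State that the multi-level model is fitted by (restricted) maximum likelihood to all observed waves of the verified dyads, under missing at random.

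Where imputation is wanted, for instance for gaps in determinants, use multiple imputation with Rubin's rules. Put the analysis variables (determinants, ethnicity and their interactions with time) in the imputation model, so that associations are not attenuated.

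A sensitivity analysis for drop-out related to unobserved outcomes is optional.

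The cost is a change of wording and slightly more analyst time; no new data are needed. Confidence intervals will be wider.
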